## 16.2 Population for analysis

The primary population will be the Intention to Treat (ITT) population defined as all patients randomized irrespective of having been administered at least one dose of randomized study medication. All primary and secondary efficacy endpoints will be analysed using this population.

The safety population will be all patients randomized and having taken at least one dose of randomized treatment. The primary endpoint will also be analysed using this population.

## 16.3 Statistical Analysis of the primary endpoint

- **Progression free survival (PFS) defined as the time from the date of randomisation to the date of first progression or death due to any cause (see [section 2.6.1.1](#))**

This endpoint will be analysed using a Cox proportional hazards model. All stratified covariates will be included in the model as well as additional covariates which are deemed to influence the response. These will be stated *a priori* in the statistical analysis plan (SAP). The 90% confidence interval for the Hazard ratio will be derived which will provide an estimate of the plausible ranges of the treatment effect. A Kaplan Meier plot of Survival probabilities over time will also be generated. Patients who take any concomitant medications which are likely to influence the primary endpoint will be censored at the date of starting the medication (if available). Patients who have not progressed or died will be censored at the last date of contact.

The primary endpoint will be analysed using both the ITT and Safety Populations. Additional analysis will be conducted as is deemed appropriate and documented in the SAP. An exploratory analysis will also be carried out using the unmodified RANO criteria (Wen et al 2010).

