#### AVF3708g and NCI 06-C-0064E studies

The AVF3708g study was a phase II trial in 167 patients (85 treated with single-agent bevacizumab) with glioblastoma at first or second relapse (Friedman, 2010). Of note only the efficacy data from the bevacizumab monotherapy arm (n=85) was used to support FDA drug approval. Findings were supported by the Phase II trial of bevacizumab in 48 patients with relapsed glioblastoma (Study NCI 06-C-0064E) (Kriesl, 2009).

- AVF3708g study - objective response rate was 28.2 % (95% CI: 18.5 -40.3%)
- AVF3708g study - median response duration was 5.6 months (95% CI: 3.0-5.8 months)
- AVF3708g study - the 6-month progression-free survival (PFS6) rate was 42.6% (97.5% CI: 29.6-55.5%)
- AVF3708g study - the 6-month PFS rates for patients at first and second relapse were 46.4% and 27.8% respectively
- AVF3708g study – the median PFS in first and second relapse was 4.4 and 3.1 months respectively
- AVF3708g study - the median overall survival was 9.2 months (95% CI: 8.2-10.7 months), median overall survival at first and second relapse was 9.1 months and 9.2 months respectively
- Study NCI 06-C-0064E - response rate was 35% percent by Macdonald criteria (one CR, 16 PRs)
- Study NCI 06-C-0064E – median PFS of 16 weeks (95% CI: 12-26 weeks)

Assuming a median PFS of 4 months with cediranib (as equivalent to bevacizumab) and an expected median PFS of 6 months on the combination cediranib plus gefitinib arm a total of 112 patients are required to achieve 110 events in order to detect a hazard ratio of about 0.67 between the two arms. This assumes an accrual period of 18 months, maximum follow up of 36 months,  $\lambda_1 = 0.115$ ,  $\lambda_2 = 0.1733$ , and a one sided type I error of 10% with approximate power of 80%. The sample size was generated using Nquery Version 7.0.

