\*In the absence of a confirmatory scan at 6 weeks later for CR or PR these should be recorded at a visit level as unconfirmed CR or PR, but the best overall response would be stable disease

For further details see the RANO criteria in Wen et al (2010).

- **PFS rate at 6 months (24 weeks)**

Progression is defined in the same way as described for the primary endpoint. This endpoint will be analysed in the same way as the primary endpoint. A comparison of the PFS rate at 6 month/ 24 weeks will be made and the 95% confidence interval will be generated for the difference in the PFS rate adjusted for any covariates. A survival plot will also be generated.

- **Overall Survival rate at 12 months.**

This will be analysed in the same way as the PFS and OS endpoints (above)

- **Time to sustained increase in total daily steroid dose by  $\geq 8\text{mg/day}$  compared to baseline or sustained nadir ( $\geq 21$  days)**

This is defined as time from randomization to first increase in dexamethasone dose. An increase in dexamethasone dose is defined as a change from the baseline of  $\geq 8\text{mg/day}$  for at least 21 days (i.e. the increase is sustained for at least 21 days consecutively). The earliest date when the dexamethasone dose was  $\geq 8\text{mg/day}$  compared to baseline or sustained nadir in this period will be used for comparison between the treatment groups. Sustained nadir refers to the highest steroid dose taken during a  $\geq 21$  days period where the patient is consistently taking a lower dose of steroids compared to the baseline dose. Daily dexamethasone dose will be recorded until progression.

This endpoint will be analysed as a time to event endpoint similarly to the OS and PFS. Additional covariates may also be included in the analyses for adjustment.

- **Average daily steroid dosage change from baseline until first progression**
- **Average number of progression/steroid free days**

For the above 2 endpoints the mean steroid dosage prior to treatment will be considered as the patient's baseline. The change in average daily steroid dosage from baseline is calculated as the mean daily dexamethasone dosage recorded from the first day of therapy to progression subtracted from baseline. If a patient does not progress, average daily steroid dosage is calculated as the mean

of daily actual dexamethasone dosage recorded prior to the last date the patient is recorded to have had a dose of dexamethasone.

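### The primary hazard ratio is reported with a 90% confidence interval that, if two-sided, does not match the one-sided 10% design, and section 16.3 names no test or success rule to settle which applies

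*Protocol*

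**What the plan says.** The sample size paragraph of protocol section 16.1 sets medians of 4 and 6 months. It states that "a total of 112 patients are required to achieve 110 events", "in order to detect a hazard ratio of about 0.67 between the two arms", with "a one sided type I error of 10% with approximate power of 80" per cent.

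Section 16.3 analyses progression-free survival with a Cox proportional hazards model adjusted for the stratification factors and further covariates to be listed in the SAP. It then says "The 90% confidence interval for the Hazard ratio will be derived", and describes that interval as showing the range of treatment effects that remain plausible. It names no hypothesis test, threshold or criterion for calling the trial positive, and does not say whether the interval is one- or two-sided.

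Section 16.8 plans no formal interim analysis. It does allow conditional power to be calculated at 50% and 75% of the required events, with a value under 20% taken as suggesting futility. It does not give the final critical value on which that conditional power would rest.

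**The concern.** The two-sided interval that mirrors a one-sided 10% test has 80% coverage. A two-sided 90% interval mirrors a one-sided 5% test. The protocol therefore fixes one error level for the design and, on the ordinary reading, a different one for the only inferential result it specifies for the primary endpoint.

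Two things are at stake. First, for a band of observed hazard ratios the two sections give opposite answers, and nothing in section 16.3 says which prevails. Choosing after the result is known would decide whether the trial is called positive. Second, conditional power is undefined without a final critical value, so the futility guide in section 16.8 inherits the same ambiguity.

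**Working it through.** **Inputs.** Section 16.1: medians 4 and 6 months, so HR = 4/6 = 0.667 and |ln HR| = ln 1.5 = 0.4055; 110 events; one-sided alpha 10%; power about 80%. Section 6.1: 1:1 allocation. Section 16.3: 90% interval, taken as two-sided (an assumption).

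**1. Reproduce the design.** Schoenfeld: events = 4(z₀.₉₀ + z₀.₈₀)² / (ln HR)² = 4(1.2816 + 0.8416)² / 0.1644 = 109.7, or 110. Power at 110 events = Φ(√(110/4) × 0.4055 − 1.2816) = Φ(2.1263 − 1.2816) = 80.1%. Freedman's formula gives 113 events and 79.3% power. The protocol's figures stand.

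**2. Critical hazard ratios.** SE(ln HR) ≈ 2/√110 = 0.1907.
- One-sided 10%: exp(−1.2816 × 0.1907) = 0.783.
- Upper limit of the two-sided 90% interval below 1 (one-sided 5%): exp(−1.6449 × 0.1907) = 0.731.

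**3. A result in the gap.** Observed HR 0.75: z = 0.2877/0.1907 = 1.51, one-sided p = 0.066, so the design test is met.
- Two-sided 90% interval: exp(−0.2877 ± 0.3137) = 0.55 to 1.03, which includes 1.
- Two-sided 80% interval: exp(−0.2877 ± 0.2444) = 0.59 to 0.96, which excludes 1.

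**4. Power if the two-sided 90% interval decided.** Φ(2.1263 − 1.6449) = 68.5%.

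| HR used | One-sided 10%, Schoenfeld / Freedman | One-sided 5%, Schoenfeld / Freedman |
|---|---|---|
| 4/6 | 80.1% / 79.3% | 68.5% / 67.5% |
| 0.67 | 79.4% / 78.6% | 67.6% / 66.6% |
| 0.115/0.1733 = 0.664 (the stated hazards) | 80.8% / 79.9% | 69.4% / 68.3% |

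At HR 4/6 the chance of landing in the gap is 80.1 − 68.5 = 11.6 percentage points. Eighty per cent power at one-sided 5% needs 4(1.6449 + 0.8416)² / 0.1644 = 150.4, or 151 events (155 by Freedman), more than the 112 patients planned.

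**5. Effect on section 16.8.** Take 55 events (50%), SE = 2/√55 = 0.2697, with Z positive in favour of the combination. Conditional power equals 20% in these cases:
- *Assumed HR 4/6:* Z√0.5 = c − 0.5 × 2.1263 − 0.8416√0.5. With c = 1.2816, Z = −0.533 and the observed HR is exp(0.533 × 0.2697) = 1.15. With c = 1.6449, Z = −0.019 and the HR is about 1.01.
- *Observed trend:* 2Z√0.5 = c − 0.8416√0.5. With c = 1.2816, Z = 0.485 and the HR is 0.88. With c = 1.6449, Z = 0.742 and the HR is 0.82.

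The same interim data could fall on either side of the 20% guide, depending on which level is meant.

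**The case against.** The strongest reply is that section 16.1 already fixes alpha and sidedness, and that not repeating them in section 16.3 does not replace them. The Cox model supplies a test of the treatment term, the interval is introduced in the language of estimation, and the details of the test can sit in the SAP, which is not shown. An interval wider than the one matching the test cannot inflate type I error; the risk is a conservative misreading. The interval is not called two-sided, and a one-sided 90% bound would match the design exactly.

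Much of this stands, and it rules out three stronger readings that a reader might draw:
- **That the stated 80% power is wrong.** It is correct for the stated alpha. The 68% applies only under a decision rule that the protocol does not contain.
- **That the 90% interval is the only inference planned.** A one-sided 10% test from the Cox model is compatible with section 16.3, although it is not written there.
- **That the 6-month comparison adds a conflicting third level,** because section 16.4 says "the 95% confidence interval will be generated for the difference in the PFS rate adjusted for any covariates". That is a secondary endpoint, and a different confidence level for it contradicts nothing.

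The reply does not remove the mismatch. The protocol chose the 90% level itself, so this is not merely detail left for later. Describing a range of plausible effects points to a two-sided interval. What section 16.3 passes to the SAP is covariates and additional analyses, not the success rule.

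**Conclusion.** The protocol is internally inconsistent on the level at which the primary result is judged. If the 90% interval is two-sided, an observed hazard ratio between about 0.73 and 0.78 meets the design criterion while the reported interval includes 1. If that interval were the decision rule, power at HR 0.667 would be about 68% (66.6% to 69.4% over the variants above). If the interval is a one-sided 90% bound, the levels agree and only the wording is unclear.

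The figures assume 110 events, SE(ln HR) of 2/√events, proportional hazards, and no change in precision from covariate adjustment. The sample size calculation needs no correction. The point ranks below a must-fix: it threatens neither type I error nor patients, but it leaves open how a borderline primary result, and a borderline futility calculation, would be called.

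**What to change.** In section 16.3, state that the primary comparison is the one-sided test, at the 10% level, of the treatment term in the Cox model, reported with the two-sided 80% interval or equivalently a one-sided 90% bound, and that any two-sided 90% interval is descriptive only. In section 16.8, state that conditional power uses the same one-sided 10% critical value.

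If the 90% figure was meant as a one-sided bound, say so. If the two-sided 90% interval is meant to decide, restate one-sided alpha as 5% and power as about 68% in section 16.1, and acknowledge that 80% power at that level would need about 151 events.

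The cost is a sentence in each section, with no extra patients or data. It should be done before any conditional power is calculated and before unblinding.

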## 16.4 Statistical Analysis of the Secondary Endpoints

The secondary endpoints will be subject to an ITT analysis only.

- **Overall survival (OS)**

This is defined as time from date of randomization to date of Death due to any cause. This endpoint will be analysed in a similar way to the primary endpoint

- **Radiographic response rate (RR) at each assessment point**

The response rates will be summarised by treatment groups in terms of counts and percentages. The following definition of responses will be used.

- **Complete response:** Requires all of the following: disappearance of all contrast enhancing lesions on MRI compared to baseline sustained for 2 consecutive 6 weekly scans\*; no new lesions; stable or improved nonenhancing (T2/FLAIR) lesions; patients must be off dexamethasone (or on physiologic replacement doses only); and stable or improved clinically. Patients with non-measurable disease only cannot have a complete response; the best response possible is stable disease.
- **Partial response:** Requires all of the following:  $\geq 50\%$  decrease compared with baseline in the sum of products of perpendicular diameters of all measureable enhancing disease percentage change sustained for 2 consecutive 6 weekly scans\*; no progression of non measurable disease; no new lesions; stable or improved nonenhancing (T2/FLAIR) lesions on same or lower dose of dexamethasone compared with the baseline scan; the dexamethasone dose at the time of the scan evaluation should be no greater than the dose at the time of baseline scan; and stable or improved clinically. Note: Patients with non-measurable disease only cannot have a complete response; the best response possible is stable disease.
- **Progression:** (See [Section 2.6.1.1](#))

**Stable Disease:** Requires all of the following: a patient whose MRI scan does not meet the criteria for *Complete Response*, *Partial Response*, or *Progressive Disease*: stable nonenhancing (T2/FLAIR) lesions on same or lower dose of dexamethasone compared with baseline scan. In the event that the dexamethasone dose was increased for new symptoms and signs without confirmation of disease progression on neuroimaging, and subsequent follow-up imaging shows that this increase in dexamethasone dose was required because of disease progression, the last scan considered to show stable disease will be the scan obtained with the dexamethasone dose was equivalent to the baseline dose.

\*In the absence of a confirmatory scan at 6 weeks later for CR or PR these should be recorded at a visit level as unconfirmed CR or PR, but the best overall response would be stable disease

For further details see the RANO criteria in Wen et al (2010).

- **PFS rate at 6 months (24 weeks)**

Progression is defined in the same way as described for the primary endpoint. This endpoint will be analysed in the same way as the primary endpoint. A comparison of the PFS rate at 6 month/ 24 weeks will be made and the 95% confidence interval will be generated for the difference in the PFS rate adjusted for any covariates. A survival plot will also be generated.

- **Overall Survival rate at 12 months.**

This will be analysed in the same way as the PFS and OS endpoints (above)

- **Time to sustained increase in total daily steroid dose by  $\geq 8\text{mg/day}$  compared to baseline or sustained nadir ( $\geq 21$  days)**

This is defined as time from randomization to first increase in dexamethasone dose. An increase in dexamethasone dose is defined as a change from the baseline of  $\geq 8\text{mg/day}$  for at least 21 days (i.e. the increase is sustained for at least 21 days consecutively). The earliest date when the dexamethasone dose was  $\geq 8\text{mg/day}$  compared to baseline or sustained nadir in this period will be used for comparison between the treatment groups. Sustained nadir refers to the highest steroid dose taken during a  $\geq 21$  days period where the patient is consistently taking a lower dose of steroids compared to the baseline dose. Daily dexamethasone dose will be recorded until progression.

This endpoint will be analysed as a time to event endpoint similarly to the OS and PFS. Additional covariates may also be included in the analyses for adjustment.

- **Average daily steroid dosage change from baseline until first progression**
- **Average number of progression/steroid free days**

For the above 2 endpoints the mean steroid dosage prior to treatment will be considered as the patient's baseline. The change in average daily steroid dosage from baseline is calculated as the mean daily dexamethasone dosage recorded from the first day of therapy to progression subtracted from baseline. If a patient does not progress, average daily steroid dosage is calculated as the mean

of daily actual dexamethasone dosage recorded prior to the last date the patient is recorded to have had a dose of dexamethasone.

The number of progression/steroid free days is the number of days that a patient is known not to have used any steroids (dexamethasone) prior to progression. This will be summarized by treatment group.

- **Time to deterioration of neurological status or death**

This endpoint will be summarized by treatment group. Neurological status based on investigator's neurological examination prior to and during treatment will be recorded on the CRF.

Patient's last pre-dose assessment will be defined as baseline. Patients without a baseline assessment will be excluded from analysis. Time to neurological status deterioration will be defined as the date of randomization to the date of first neurological status worsening in comparison to baseline (first of 2 confirmatory reports at 2 consecutive visits, 6 weeks apart) as assessed by the clinician, or until date of death, whichever is first.

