### 2.5.2 Secondary Objectives

- To document the safety and tolerability of cediranib in combination with oral gefitinib and cediranib alone.
- To compare cediranib in combination with oral gefitinib and cediranib alone in terms of steroid sparing effects
- To document the quality of life and neurological symptoms reported by patients taking cediranib in combination with oral gefitinib and cediranib alone.
- To investigate the relationship between the effects of cediranib (+/- gefitinib) on levels of soluble angiogenesis biomarkers and clinical efficacy
- To investigate the relationship between the patient's genetic profile and efficacy of cediranib (+/- gefitinib)

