#### 5.1.1 Inclusion Criteria

For inclusion in the clinical trial, patients must fulfil all of the following criteria:

- Provision of informed consent
- Age  $\geq 18$  years
- Life expectancy  $\geq 12$  weeks
- Histological/cytological confirmation of glioblastoma (WHO grade IV)
- Patients with measurable disease (contrast-enhancing tumour  $\geq 10$  mm by shortest diameter on 2 axial slices) by MRI imaging within 7 days prior to enrolment. (If patients have recently had a routine MRI scan, this should be assessed before deciding whether or not to screen the patient, and booking the screening/baseline MRI.)
- Patients must have been on no steroids or a stable dose of steroids (dexamethasone) for at least 5 days before the baseline MRI
- Patients must have completed standard first-line treatment for glioblastoma including surgery (with exception, if patient does not receive surgery as part of first-line treatment due to anatomical location, based on neurosurgeon's assessment), cranial radiotherapy and chemotherapy with concomitant temozolomide.
  - It is not essential that the entire Stupp regimen of 6 cycles of adjuvant temozolomide following chemoradiotherapy has been completed.
  - The last dose of temozolomide must be more than 28 days from enrolment.
  - Gliadel® wafers are permitted, as it is part of local treatment.
  - No other previous treatment for glioblastoma is permitted (other than steroids).

- Patients must have a Karnofsky Performance Score of 70 or above
- Patients must have a mini-mental status examination score of 15 or greater
- Patients who require either oral anticoagulants (coumadin, warfarin) or low molecular weight heparin are eligible provided there is increased vigilance with respect to monitoring INR.

For inclusion in the genetic research, patients must fulfil the following criterion:

- Provision of informed consent for genetic research (separate consent required for tumour biopsy, blood sample, and post mortem donations)

If a patient declines to participate in any of the genetic research, there will be no penalty or loss of benefit to the patient. The patient will not be excluded from other aspects of the study described in this Clinical Study Protocol, so long as they consent to the main study.

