#### **h) Follow up assessment schedule after discontinuation**

If a patient discontinues due to reasons other than progression, the patient will continue to be followed-up every 6 weeks until progression or death. If a patient discontinues due to progression, or has progressed after discontinuation, the patient will continue to be followed-up every 12 weeks for survival (via telephone call). All efforts should be made by the Site to contact the patient's GP to assess their condition, if a patient fails to attend a clinic or cannot be followed up at site. The trial will be registered with the NHS Information Centre in the event that any patients become Lost to Follow Up.

Neurological status assessments should be continued until neurological deterioration has been documented on 2 consecutive 6 weekly assessments. Dexamethasone dose per day should be collected until progression documented (as outlined in [section 2.6.1.1](#))

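### Average daily steroid dose is averaged over a shorter window in patients who do not progress, so steroid-free days after their last dose are lost; few patients are affected on the planned follow-up

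*Protocol*

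**What the plan says.** Section 2.5.2 of the protocol makes it a secondary objective to compare the arms "in terms of steroid sparing effects". Section 2.6.1.2 lists change in average daily steroid dose up to first progression among the outcomes that serve it.

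Section 16.4 defines the calculation. For the baseline, "the mean steroid dosage prior to treatment will be considered as the patient's baseline". For patients who progress, the change uses "the mean daily dexamethasone dosage recorded from the first day of therapy to progression subtracted from baseline". For patients who do not progress, the average is instead the mean "of daily actual dexamethasone dosage recorded prior to the last date the patient is recorded to have had a dose of dexamethasone". No start date is given for this second window.

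The companion endpoint in the same block, progression/steroid-free days, counts the "number of days that a patient is known not to have used any steroids (dexamethasone) prior to progression".

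On data collection, section 8.2 note h states: "Dexamethasone dose per day should be collected until progression documented". Daily dose is also an item at every on-treatment visit in section 8.1 and is recorded in the patient diaries (section 8.3).

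**The concern.** The two windows treat zero-dose days differently. In a patient who progresses, every day between start of therapy and progression enters the denominator, whether or not dexamethasone was taken. In a patient who does not progress, the window closes at the last day a dose was taken, and the steroid-free time after it disappears. The denominator therefore depends on the outcome.

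The days lost belong to patients who are both progression-free and off steroids, the very pattern the endpoint is meant to credit. Any distortion works against the arm with more such patients.

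There is also a gap. Section 5.1.1 admits patients on no steroids ("Patients must have been on no steroids or a stable dose of steroids (dexamethasone) for at least 5 days before the baseline MRI"). A non-progressor who never takes dexamethasone has no last-dose date, so the mean is undefined. Section 16.7 leaves missing values missing, so such a patient would drop out of an endpoint that section 16.2 assigns to the intention-to-treat population.

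**Working it through.** **1. Same course, two scores.** The dose courses and follow-up times are illustrative assumptions. The non-progressor window is taken to start on the first day of therapy.

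- Course A: 4 mg/day for 21 days, then none, followed to day 200. Total dose 4 × 21 = 84 mg.
  - Progresses on day 200: 84/200 = 0.42 mg/day.
  - Does not progress: 84/21 = 4.0 mg/day.
  - Difference: 4.0 − 0.42 = 3.58 mg/day.
- Course B, abrupt stop: 8 mg/day (the highest dose section 5.1.2 allows at entry) for 14 days, then none to day 168.
  - Section 16.4 rule without progression: 8.00 mg/day, so the change from a baseline of 8 is 0. This equals the score of a patient on 8 mg for all 168 days.
  - Full window: 112/168 = 0.67 mg/day, change 7.33.
- Course C, taper: 8, 4 and 2 mg/day for 14 days each, then none to day 168. Total 112 + 56 + 28 = 196 mg.
  - Section 16.4 rule without progression: (196 − 2)/41 = 4.73 mg/day (196/42 = 4.67 if the last dose day is included), change 3.27.
  - Full window: 196/168 = 1.17 mg/day, change 6.83. The rule drops 168 − 42 = 126 days.
  - With 84 or 336 days of follow-up the rule still gives 4.73, while the full-window mean is 2.33 or 0.58.

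Zero-dose days that fall before a later dose are kept. Only those after the final dose are lost.

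**2. How many patients.** The protocol gives no figure for this endpoint, so the number of non-progressors comes from section 16.1: 112 patients, 110 events, hazard ratio about 0.67, one-sided 10% error, about 80% power, accrual 18 months, maximum follow-up 36 months, hazards 0.115 and 0.1733 per month.

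Reproducing the event count (Schoenfeld): 4 × (1.2816 + 0.8416)² / [ln(4/6)]² = 18.03/0.1644 = 109.7, or 110. This agrees with the protocol.

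Event-free fraction with exponential times and uniform accrual (A = 18, T = 36):

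[exp(−λ(T − A)) − exp(−λT)] / (λA)

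- Combination, λ = 0.115: 0.0533, × 56 = 2.98 patients.
- Cediranib plus placebo, λ = 0.1733: 0.0135, × 56 = 0.76 patients.
- Total about 3.7 of 112 (108.3 expected events). The protocol's own 110 events would leave 2.

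**3. Arm-level size.** If every event-free patient followed course A, the spurious between-arm difference would be (2.98 − 0.76) × 3.58/56 = 0.14 mg/day. Each affected patient moves an arm mean by 3.58/56 = 0.06 mg/day under course A, or 7.33/56 = 0.13 mg/day under course B.

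**The case against.** The strongest case on the other side is about size and intent.

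- **Few patients are non-progressors.** Section 2.6.1.1 treats failure to return because of death or deterioration as progression and lets death set the progression date. Section 8.2 note h continues follow-up to progression or death after treatment stops for other reasons, and lost patients are traced. Most patients therefore fall under the rule that counts zero-dose days. This stands, and it is why the effect is small.
- **Steroid sparing has other endpoints.** Steroid-free days are counted directly in the companion endpoint, and time to sustained steroid increase is untouched. This stands as mitigation, but neither puts the dropped days back into the average dose.
- **It may be a drafting slip.** The authors may have meant the last date with a dose record, zeros included. That is possible, but the wording refers to having had a dose, and the sentence needs correcting on either reading.

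A reader might infer that anyone who tapers is scored as a continuous user. The text does not support that. Only an abrupt stopper scores exactly like one. A gradual taperer scores the mean dose while on drug, which in course C is still a reduction from baseline (3.27 rather than 6.83 mg/day).

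**Conclusion.** The rule is wrong as written. It gives different values for the same steroid course according to outcome and leaves non-progressing never-users without a value. The protocol states this rule itself, so it is not a detail left to a later analysis plan.

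The severity is minor. On the planned hazards and follow-up, about 3 to 4 patients would be event-free, and the between-arm distortion is about 0.1 mg/day even if all of them followed course A. That figure rests on exponential event times, uniform accrual, full follow-up and an invented dose course. An earlier data cut or more loss to follow-up would increase it.

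A reader might suppose that something like 5 to 15% of the trial (6 to 17 patients) is affected, or read the roughly tenfold gap in course A as the bias in the endpoint. Neither is supported: section 16.1 implies about 3%, and the tenfold gap describes one constructed patient, not an arm mean. The primary endpoint and its power are unaffected.

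**What to change.** Replace the sentence for non-progressors in section 16.4 with one rule for all patients: the mean daily dexamethasone dose from the first day of therapy to the earliest of progression, death or last dexamethasone assessment, with recorded steroid-free days counted as 0 mg and patients who never took dexamethasone scored 0.

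The cost is one sentence. The daily doses are already collected, so no new data are needed. Only the analysis definition of a secondary endpoint changes.
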